# A pilot study to evaluate the effect of Taeumjowi-tang on obesity in Korean adults: study protocol for a randomised, double-blind, placebo-controlled, multicentre trial

**DOI:** 10.1186/1745-6215-13-33

**Published:** 2012-04-07

**Keywords:** Taeumjowi-tang, obesity, efficacy, safety, randomised controlled trial

## Abstract

**Background:**

Obesity, which is described as excessive or abnormal body fat, increases the risk of diet-related diseases. In Korea and around the world, the prevalence of obesity has grown annually from 1998 to 2008. This growth has continued despite various therapeutic efforts. The discovery of new and alternative treatments for obesity should be considered an important priority. Taeumjowi-tang (TJ001), a traditional Korean medicinal extract consisting of eight herbs, is a widely used herbal remedy for obesity in Korea. However, the efficacy and safety of TJ001 have not been fully investigated in a clinical trial. The purpose of this pilot study is to estimate obesity-related parameters and to assess the efficacy and safety of TJ001.

**Methods:**

Our study is a randomised, double-blind, placebo-controlled, multicentre clinical trial of Taeumjowi-tang (TJ001). For this study, we will recruit obese Korean patients of both sexes, ages 18 to 65 years, from four university hospitals. A total of 104 subjects will be recruited. The participants will receive either 7 g of TJ001 or a placebo three times daily for 12 weeks. The primary end point will be the rate of subjects who lose at least 5% of their baseline body weight. The secondary end points will be changes in body weight, body mass index, waist circumference, hip circumference, waist/hip circumference ratio, lipid profiles, body fat composition, blood pressure, fasting glucose concentration, C-reactive protein and questionnaires related to the quality of life. The outcomes will be measured every 4 weeks. The study period will be 12 weeks and will include a total of five visits with each subject (at screening and at 0, 4, 8 and 12 weeks).

**Conclusions:**

The results of our study will inform various estimates of TJ001 and will serve as the basis for a larger-scale trial. This study will assess the efficacy and safety of TJ001 as an alternative herbal remedy for obesity.

**Trial registration:**

Current Controlled Trials ISRCTN87153759

## Background

The World Health Organisation (WHO) defines "obesity" as abnormal or excessive fat accumulation that may impair health [1]. Treatment of obesity is important because this chronic, noncommunicable disease causes not only a range of health problems, such as cardiovascular disease, various metabolic syndromes and certain cancers [1-3], but also social problems. In addition to the global incidence of obesity, obesity has become one of the most life-threatening problems in Korea. The Korea National Health and Nutrition Examination Survey showed that the overall prevalence of Korean adult obesity in 2008 was 30.7%, compared with 21.8% in 1998 [4]. The survey defined adults as individuals who are at least 20 years old, and obesity was defined as a body mass index (BMI) 25 kg/m^2 ^according to the definition of the International Association for the study of Obesity in the Western Pacific Region of the WHO [1,5].

Several nonpharmacological attempts to curb the increase in obesity, including dietary or exercise management, have been largely unsuccessful. These failures have encouraged specialists to develop treatments using pharmacotherapy [2]. Despite these therapeutic attempts, an efficacy and safety limit for conventional weight reduction therapies is apparent [6]. The demand for safe and effective anti-obesity agents is increasing, and herbal combinations are meeting those needs [7]. The relative importance and potential benefits of herbal preparations has extended their role as possible alternative methods for obesity therapies.

Taeumjowi-tang (TJ001; HANPOONG Pharm & Foods Co Ltd, Jeonju-si, South Korea) is a traditional Korean medicine preparation that originated from I Je-ma's Sasang constitutional medicine theory [8]. This theory is representative of the individualised medical approach, which is widely used to diagnose and treat disease in Korea. The Sasang typology explains specific disease susceptibility and drug response differences through distinctive pathology types. Taeumjowi-tang (TJ001) is a decoction consisting of eight herbal ingredients and is usually prescribed for Tae-Eum persons (Greater Yin person, or Tae-Eum-In) to regulate stomach-related symptoms such as jaundice, anhidrosis, stuffiness and the sensation of fullness [8-10]. Owing to the unique pathology of Tae-Eum, these individuals gain weight more easily than the other three constitutional types (Tae-Yang, So-Eum and So-Yang). The Sasang typological formulary for Tae-Eum persons contains many therapies related to obesity. Among the various preparations, TJ001 has become the treatment regimen for obesity most widely used by Korean medical professionals [11-15], and its use has been expanded to all types of obesity. Preclinical results have supported the antiobesity and hypolipidaemic effects of TJ001 [16-19]; however, the results of clinical studies have been insufficient [20,21]. Although many large, placebo-controlled trials of herbal combinations and dietary supplements showing antiobesity effects have been reported [22-27], large-scale trials of Taeumjowi-tang have not yet been conducted.

This study will be the first reported randomised, double-blind, placebo-controlled clinical trial of Taeumjowi-tang (TJ001) in obese adults in Korea. The main purpose of this study is to assess the efficacy and safety of medicinal herbal extract of Taeumjowi-tang through a 12-week randomised controlled trial (RCT) that produces obesity-related estimates.

## Methods

### Objectives and hypothesis

#### Objectives

The main objectives of this trial are to (1) evaluate the efficacy and safety of TJ001 in obese Korean adults, (2) explore estimates of obesity-related variables, including the amount of weight reduction, (3) discover the precise target population, (4) establish an appropriate primary end point and (5) estimate the proper treatment period.

#### Hypothesis

We hypothesise that the TJ001 responder rates with a 5% or greater weight reduction will be higher than those in the placebo group. We also expect that use of TJ001 will be relatively safe.

### Study design and period

This study is a 12-week randomised, double-blind, placebo-controlled, multicentre trial at four tertiary university hospitals. Figure 1 shows the schematic flow of the study.

**Figure 1 F1:**
[figure not shown]
**Flowchart of the Taeumjowi-tang (TJ001) clinical trial**.

### Study groups

The study will include the following two arms: the TJ001 group (treatment arm) and the placebo group (control arm).

### Population

The subjects will be obese Koreans of both sexes and ages 18 to 65 years.

### Eligibility criteria

#### Inclusion and exclusion criteria

The inclusion and exclusion criteria are shown in Table 1.

**Table 1 T1:** Inclusion and exclusion criteria^a^

Criteria
**Inclusion criteria**

1. Men and women ages 18 to 65 years
2. Individuals who meet one of the following criteria:
2.1. BMI ≥ 30 kg/m^2^
2.2. BMI 27 to 30 kg/m^2 ^with hypertension at a proper treatment- and blood pressure-controlled 95 to 145 mmHg
2.3. BMI 27 to 30 kg/m2 with non-insulin-dependent diabetes mellitus and fasting blood glucose < 7.8 mmol/L (140 mg/dl)
2.4. BMI 27 to 30 kg/m2 with hyperlipidaemia in a proper treatment regimen
2.5. BMI 27 to 30 kg/m2 and ≥ 236 mg/dl total cholesterol or ≥ 150 mg/dl triglycerides at screening
3. Agreed to low-calorie diet during the trial
4. Written informed consent for participation in the trial
5. Written informed consent for the genetic test
Exclusion criteria
1. Endocrine disease such as hypothyroidism or Cushing syndrome
2. Heart disease (heart failure, angina pectoris and/or myocardial infarction)
3. Uncontrolled hypertension (SBP > 145 mmHg or DBP > 95 mmHg)
4. Malignant tumour or lung disease
5. Cholelithiasis
6. Severe renal disability (sCr > 2.0 mg/dl)
7. Severe liver disability (2.5-fold the normal high range value for ALT, AST and ALP)
8. Non-insulin-dependent diabetes mellitus and fasting blood sugar 7.8 mmol/L (140 mg/d or over
9. Narrow-angle glaucoma
10. History or existence of neurological or psychological disease (schizophrenia, epilepsy, alcoholism, drug addiction, anorexia, bulimia and so on)
11. History of stroke or temporary ischaemic cardioplegia
12. History or existence of eating disorder such as anorexia nervosa or bulimia nervosa
13. Use of medication within the past 3 months that could have an effect on weight (appetite suppressant, laxative, oral steroid, thyroid hormone, amphetamine, cyproheptadine, phenothiazine or medication having an effect on absorption, metabolism and excretion)
14. Use of β-blocker or diuretic as hypertension medication within the past 3 months
15. Use of central nervous system medications or central nervous system stimulating weight reduction medications
16. Forbidden treatments (insulin, hypoglycaemic agent, antidepressant, antiserotonin agent, barbiturate, antipsychotic and concerns related to medication abuse)
17. Difficult-to-measure anthropometric dimensions due to anatomical changes such as resection surgery
18. History of weight reduction surgery, bariatric surgery and so on
19. Unable to follow instructions during the trial as judged by the investigator
20. Women who are pregnant, lactating, planning a pregnancy or women of child-bearing age who do not agree to proper contraception (birth control pill, hormone implant, IUD, spermicide, condom, abstinence and so on) (women of child-bearing age indicated to be within 2 years of menopause who did not receive hysterectomy, bilateral tubal ligation, bilateral oophorectomy, and so on)
21. Use of other investigational products within the past month
22. Weight reduction > 10% within the past 6 months
23. Cessation of smoking within past 3 months or an irregular smoking habit

^a^*ALP *alkaline phosphatase, *ALT *alanine aminotransferase, *AST*aspartate aminotransferase, *BMI *body mass index, *DBP *diastolic blood pressure, *IUD *intrauterine device; *SBP *systolic blood pressure, *sCr*, serum creatinine

#### Subject withdrawal criteria

The subjects who meet the criteria listed in Table 2 will be discontinued from treatment. The participants who will be withdrawn after randomisation will be followed for outcomes.

**Table 2 T2:** Subject withdrawal criteria

Subject withdrawal criteria
1. Protocol violation: detection of eligibility violations, poor compliance (mean compliance < 70% at the last estimation) or noncompliance, use of any forbidden medication or treatment during the trial that could affect the study results, occurrence of other significant protocol violation during the trial
2. Occurrence of a serious adverse event
3. Subject has an acute reaction (allergy, shock and so on) to the investigational product
4. Detection of a systemic disease that was not discovered at the screening stage
5. Unable to progress because of worsening of preexisting disease
6. Subject's withdrawal of consent
7. Subject is uncooperative
8. Investigator's decision to terminate the process for the sake of the subject's health

### Interventions

Participating subjects assigned to either the treatment group or the placebo group will be instructed to take 7 g of TJ001 or placebo three times daily (a total of 21 g) for 12 weeks (84 days). TJ001 (Taeumjowi-tang granule extract, HANPOONG Pharm & Foods Co Ltd) is a compound of the powdered extract of several medicinal herbs, and the placebo will be similar to TJ001 in form, colour and odour. The components of TJ001 and the placebo are listed in Table 3.

**Table 3 T3:** Constituents of interventions (TJ001 and placebo)^a^

	**TJ001 granule extract**^**b**^		
**Name of herb**	**Raw material code**	**Dose (g)**	**Content (%)**

*Semen Coicis*	M040487	3.75	NA
*Semen Castaneae*	M089646	3.75	NA
*Semen Raphani*	M210181	2.5	NA
*Schisandrae Fructus*	M040445	1.25	NA
*Liriopis tuber*	M040139	1.25	NA
*Herba Ephedrae*	M040135	1.25	NA
*Radix platycodi*	M040048	1.25	NA
*Acori Tatarinowii Rhizoma*	M051377	1.25	NA
	**Placebo**		
**Composition**	**Raw material code**	**Dose**	**Content (%)**
Lactose	NA	NA	87.99%
Starch	NA	NA	11.73%
Food colouring	NA	NA	0.28%

^a^*NA *not applicable. ^b^Korea Ministry for Health and Welfare classification 233 (ATC code A16AX).

### Lifestyle management

Dietary intake and the type and intensity of exercise will be recorded by the research coordinator at every visit but will not be managed strictly.

#### Dietary instructions

For dietary counselling, the subjects will be counselled to consume 20 to 25 kcal/kg. In other words, the participants will be asked to keep their dietary intake approximately at 1,500 kcal/day for men and 1,200 kcal/day for women. A dietary intake diary will be distributed to the subjects, and they will use a diary to calculate the number of calories consumed.

#### Exercise

As the trial will be conducted without lifestyle management, the participants will be allowed to maintain their usual exercise levels. However, intense, unusual workouts will not be permitted.

### Concomitant treatments and forbidden drugs

The subjects will be permitted to use medications only with the investigator's permission. The product name, use, dosage and duration of these medications will be recorded. The following concomitant treatments will be prohibited: central nervous system medications; central nervous system stimulating weight reduction medications; medications that could have an effect on weight (insulin, hypoglycaemic agents, oral steroids, thyroid hormones, cyproheptadine and phenothiazine); medications that affect absorption, metabolism or excretion; β-blockers and diuretics for hypertension treatment; amphetamines; antidepressants; antiserotonin agents; barbiturates; antipsychotics; and medicines that increase blood pressure or pulse, including decongestants that contain phenylpropanolamine, ephedrine or pseudoephedrine as well as medicines for coughs, common colds and allergies.

### Sample size calculation

A sample size of 104 subjects was estimated for 80% power at a significance level of 0.05 and an attrition rate of 20%. Participants will be selected according to the eligibility criteria.

No preliminary studies of TJ001 were available to aid in estimating the percentage of subjects with 5% or greater weight loss [21]. Therefore, we set the rate at 40% for the TJ001 group and 13% for the placebo group on the basis of a reference paper [28]. The formula for calculating the sample size when allocating subjects at a ratio of 1:1 (TJ001:placebo) is as follows:

$$\begin{array}{c} n=\frac{{\left\{z_{1-\alpha }\sqrt{2\bar{p}\left(1-\bar{p}\right)}+z_{1-\beta }\sqrt{p_{t}\left(1-p_{t}\right)+p_{c}\left(1-p_{c}\right)}\right\}}^{2}}{{\left(p_{t}-p_{c}\right)}^{2}}\\ \;=\frac{{\left\{1.96\sqrt{2\left(0.265\right)\left(0.735\right)}+0.84\sqrt{\left(0.40\right)\left(0.735\right)+\left(0.13\right)\left(0.87\right)}\right\}}^{2}}{{\left(0.40-0.13\right)}^{2}}\approx 41 \end{array}$$

p_t_

The 5% or greater responder rate of the initial weight in TJ001 group = 40%.

p_c_

The 5% or greater responder rate of the initial weight in the placebo group = 13%.

$$\bar{p}:\left(p_{t}+p_{c}\right)/2=26.5\%\;z_{1-\alpha /2}=1.96,\;z_{1-\beta }=0.84$$

Allowing for an attrition rate of 20%, the number of subjects in each group is 52.

$$n^{*}=\frac{n}{\left(1-0.2\right)}=51.25\approx 52$$

Therefore, a total of 104 subjects are needed for this trial.

### Randomisation method

The study subjects who satisfy the eligibility criteria will be randomised using a web-based randomisation program at an independent centre (Medical Research Collaborating Center of Seoul National University Hospital http://mrcc.snuh.org/). This program will be set to allocate participants equally to each site at a ratio of 1:1. Each of the four sites will be allocated 26 participants. The TJ001 and placebo groups will each be allocated 52 participants. The randomisation program will be designed with a four-patient block randomisation.

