### Statistical analysis

#### Efficacy assessment

The primary outcome will be analysed using the intention-to-treat (ITT) method. The secondary outcomes will be assessed by both the ITT and the per-protocol (PP) methods. The full analysis set for ITT method will include all randomised subjects, regardless of their subsequent withdrawal after enrolment. The PP analysis will include patients who have completed the 12-week study term without any major protocol violations and have a compliance rate > 70%. Missing values will be replaced by using the last observation carried forward method. Continuous variables will be reported as means ± SD, and categorical variables will be reported as percentages. The baseline characteristics will be compared by either Student's *t*-test for continuous variables or the χ^2 ^test (Fisher's exact test when the expected value is < 5) for categorical data. Alternatively, McNemar's test will be used if the normality assumption is not satisfied for the continuous variables.

For the within-group analyses, primary and secondary outcome variables will be evaluated by using a paired *t*-test. Alternatively, for nonnormal distribution data, the Wilcoxon test will be performed. Analysis of covariance will be applied to analyse differences in each group at every visit, adjusting for age, baseline weight and BMI as covariates. Between-group comparisons for each variable will be performed using Student's *t*-test. Statistical significance will be defined as *P *< 0.05. PASW for Windows version 18.0 software (SPSS, Inc, Chicago, IL, USA) will be used for the analyses.

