## Trial status

The trial was first designed in 2009, and the study began the same year. The study is ongoing, and subject recruitment has not been completed.

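### Blocks of four in sites of 26 do not guarantee the stated equal split, and no described analysis includes site, the factor on which allocation appears to be balanced

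*Protocol article*

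**What the plan says.** All the allocation statements are in the protocol article under Randomisation method. On the role of site: "This program will be set to allocate participants equally to each site at a ratio of 1:1". On numbers: "Each of the four sites will be allocated 26 participants" and "The TJ001 and placebo groups will each be allocated 52 participants". On the mechanism: "The randomisation program will be designed with a four-patient block randomisation". The natural reading is that blocks run separately in each site, but the section does not say so and does not call site a stratum.

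On analysis, Efficacy assessment describes an ANCOVA "adjusting for age, baseline weight and BMI as covariates" and an unadjusted Student's t-test between groups. It names χ² or Fisher's exact test for categorical baseline characteristics, and does not clearly name the between-group test for the binary primary outcome. The Discussion adds an analysis stratified by sex and repeats age, weight and BMI as the covariates. Site appears in none of these.

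**The concern.** Two things do not fit together. First, a block of four does not divide 26, so the block size, the site size and the equal split are not jointly assured, although the equal split is written as a fixed result.

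Second, the article commits to a list of adjustment factors that were not used in allocation and leaves out the one on which allocation appears to be balanced. Balancing on a factor removes its contribution to the difference between arms. An analysis that ignores the factor still counts that contribution as noise. If site predicts response, the standard error is then too large, type I error falls below the nominal 5%, and some power is given away in a trial of only 104. Site differences are plausible. Recruitment lists one hospital in Seoul, two in satellite cities and one in a midsized city, three of them oriental medicine hospitals, and Lifestyle management says diet and exercise will not be strictly managed.

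**Working it through.** **Inputs from the article.** Block size 4; 26 per site; 4 sites; 52 per arm; two-sided 5% level (z = 1.96); and "we set the rate at 40% for the TJ001 group and 13% for the placebo group". The documents give no figure for the spread of responder rates across sites, so that is assumed below.

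**The plan's own figure.** With p̄ = (0.40 + 0.13)/2 = 0.265:

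n = {1.96·√(2 × 0.265 × 0.735) + 0.84·√(0.40 × 0.60 + 0.13 × 0.87)}² / 0.27² = 40.7, so 41 per arm; 41/0.8 = 51.25, so 52 per arm and 104 in total.

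This agrees with the article. (Its worked line prints 0.735 in place of 0.60 in the second root, which would give 42.5. The stated 41 follows from 0.60.)

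**Split if blocks run within site.** 26 = 6 × 4 + 2: six full blocks give 12:12, then half of a 2:2 block is used. Of the 6 equally likely pairs for two of four places, 4 are one of each arm and 1 is both of either arm. So a site ends 13:13 with probability 2/3, 14:12 with 1/6 and 12:14 with 1/6.

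- All four sites 13:13: (2/3)⁴ = 0.198.
- Total 52:52: (2/3)⁴ + 12 × (1/36) × (4/9) + 6/1296 = 0.1975 + 0.1481 + 0.0046 = 0.350.
- Total 51:53 or 53:51: 0.469. Total 50:54 or 54:50: 0.154.
- Worst case 48:56 or 56:48: 2 × (1/6)⁴ = 0.0015.

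**Split if one sequence runs across sites.** 104/4 = 26 full blocks, so 52:52 is certain at full recruitment, but nothing then holds each site at 13:13.

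**Cost of the imbalance.** Normal approximation, all randomised counted:

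power = Φ{[0.27 − 1.96·√(p̄(1 − p̄)(1/n_t + 1/n_c))] / √(0.24/n_t + 0.1131/n_c)}.

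- 52:52: (0.27 − 0.1696)/0.0824 = 1.218, power 88.8%.
- 56 on TJ001 and 48 on placebo: p̄ = 0.275, (0.27 − 0.1722)/0.0815 = 1.200, power 88.5%.
- The reverse split: 88.8%.

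The loss is at most about 0.3 points.

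**Cost of leaving out site.** 200,000 simulated trials per scenario, blocks of four within site, 26 per site. The comparison is a pooled χ² test without site against a Cochran-Mantel-Haenszel (CMH) test by site. Site log-odds are spread evenly with the SD shown. Type I error uses a common mean rate of 26.5% in both arms; power uses mean rates of 40% and 13%.

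| SD of site log-odds | Site rates at mean 26.5% | Type I, no site | Type I, CMH | Power, no site | Power, CMH |
|---|---|---|---|---|---|
| 0 | 26.5% throughout | 5.1% | 5.0% | 89.7% | 89.4% |
| 0.3 | 19.1% to 34.6% | 5.0% | 5.0% | 90.0% | 90.0% |
| 0.5 | 14.8% to 40.0% | 4.7% | 5.0% | 90.3% | 90.8% |
| 0.8 | 9.6% to 47.7% | 4.0% | 5.0% | 91.0% | 92.3% |
| 1.2 | 5.0% to 56.8% | 3.0% | 5.0% | 91.8% | 94.5% |

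At a common rate of 13% the test without site gives 4.9%, 4.8%, 4.6%, 4.2% and 3.7% down the same rows.

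A large-sample check agrees closely. The true variance relative to the pooled one is 1 − Var(site rates)/(0.265 × 0.735). At SD 1.2 this is 1 − 0.0394/0.1948 = 0.80, so type I error is about 2Φ(−1.96/√0.80) = 2.8%. At SD 0.5 the ratio is 0.954 and the result is 4.5%.

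**The case against.** Several stronger conclusions are tempting, and the documents do not support them.

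- A reader might infer that the stated split is impossible. It is only not guaranteed: 52:52 occurs in 35% of cases with blocks within site and is certain with one sequence across sites, a reading that the text does not exclude.
- A reader might infer that the planned test is conservative as it stands. That depends on sites differing in response. The article gives a single placebo rate and describes all four sites as tertiary university hospitals. Up to an SD of 0.5, where the odds of response already differ almost fourfold between the extreme sites (0.400/0.600 against 0.148/0.852), type I error stays close to 5%. The error is also in the safe direction.
- A reader might infer a larger loss. Placebo rates of 3%, 5%, 14% and 30% with a constant odds ratio of 4.46 give 77.7% power without site against 82.0% with it. Those rates are invented, so this cannot be taken as the size of the problem.
- A reader might infer that the published block size threatens concealment, since the article also says: "The study is ongoing, and subject recruitment has not been completed". Knowing the block size helps only someone who has already recognised earlier assignments. Allocation is web-based at an independent centre and product is labelled by code. The article matches the placebo on form, colour and odour and is silent on taste, but nothing says that taste differs.

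It can also be said that a site term is commonly left to an analysis plan, which is not shown here, and that the χ² comparator is an assumption. Both are fair and limit the weight of the point. They do not remove it: the article fixes an explicit set of factors in two places, and site is in neither. The Discussion's argument that strata cost power concerns randomising by sex, age, weight and BMI, not site.

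**Conclusion.** The point holds in a limited form. Block size, site size and equal split are not jointly guaranteed on either reading of the randomisation text, with a power cost of at most about 0.3 points. Leaving site out of the described analyses is a mild inefficiency, conditional on responder rates differing by site. Over an assumed SD of site log-odds of 0.5 to 1.2, type I error is about 4.7% to 3.0% and the power lost is about 0.5 (90.8 − 90.3) to 3 points (94.5 − 91.8 = 2.7). With similar sites there is no material effect. These figures assume blocks within site, a χ² test of the primary outcome and all 104 analysed. Nothing here inflates false positives or invalidates the sample size of 104. The reason to act is that the remedy is nearly free.

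**What to change.** 1. Analyse the primary outcome with a Cochran-Mantel-Haenszel test stratified by site, or with logistic regression including site, and add site to the ANCOVA models.
2. State under Randomisation method whether the blocks run within each site or in one sequence across sites.
3. Describe 13:13 per site and 52:52 overall as targets, not as assured splits.

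The cost is a few sentences. If sites turn out to be identical, stratifying gives up about 0.3 points of power in the simulation above (89.7% against 89.4%), and at most about half a point.

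Changing the block sizes for the remaining allocations is optional and not needed for this fix. Blocks of 2 would divide 26 exactly, but they are easier to predict for anyone who recognises a product, and study product is already labelled by randomisation code, so a change in mid-trial could mean relabelling.
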